### Sample size, recruitment, participants and allocation

3.3

Prior to starting the present study, a power analysis was performed (G*Power 3; Heinrich-Heine-Universität, Düsseldorf, Germany) to calculate the adequate sample size (F-test, effect size = 0.25, α error = 0.05, power = 0.95). According to this calculation, the participation of 54 students is estimated. Being an experimental study, the sample is not large, however it has great power and can be representative of this group of students (30).

The eligible school directors will be invited to participate initially by e-mail and then they will be contacted a week later by telephone. A researcher will meet with all the interested directors to explain the requirements for participation in the study. Then, be organized a presentation day to explain the project to the teachers and students. Those who agree in include their schools in the study will receive a statement in simple language and a consent form to be signed. The recruitment lasts 2 months and will be during the year 2024. Finally, the study setting is two primary school in the city of Valparaíso, Chile.

Once the consent of the school authorities has been obtained, the consent in writing for the elementary classroom teachers to participate will be obtained, since the intervention will be part of the daily class activities. Afterward, all the children in the participating courses will receive a document with the information regarding the program containing a declaration in simple language, a consent form for the parents or guardians, and an assent form confirm the children’s participation. After this authorization, the ACTIVA-MENTE program will be carried out with all the children in the classes, but only data from children which the parents’ consent and their assent of participation will be compiled. The participation in the program will be volunteer and if the children are free to decide to give in the program whenever they want.

The randomization will be carried out by a blind researcher who has no contact with the schools or participants, using a random numerical sequence generated by the Oxford Minimization and Randomization (OxMaR) computer program (31). All the schools will be from areas of a middle socioeconomic position in a similar geographic location, avoiding great differences between the groups baseline characteristics (Figure 2). Possible differences identified between the intervention and the control groups will be adjusted in the statistical analyses to not influence the results.

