### Study design

3.1

The study is carried under a quantitative method. This study uses an experimental design with a pre-and post-test. The sample will be divided into two groups: intervention and control. An active break program - ACTIVA-MENTE – will be applied to the intervention group in their respective classes during the school day for 6 weeks, while the control group will perform their regular school day (without any intervention).

The protocol was developed in agreement with Standard Protocol Items: Recommendations for Interventional Trials (SPIRIT) and according to the verification guidelines of Consolidated Standards of Reporting Trials (CONSORT). Figure 1 provides a general description of the chronogram of enrolment, interventions and assessments.

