### Procedures, outcomes measures and data collection

3.7

Three measurements will be assessed at weeks 1, 3 and 6: physical activity levels, on-task classroom behavior and enjoyment of physical activity. The implementation will be carried out by a group of research collaborators properly trained by the research team during four sessions previous to the assessment on the application of the instruments. The evaluators do not know the students and in the research, they only carry out the data collection.

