#### Secondary outcome: physical activity enjoyment

3.7.3

The Physical Activity Enjoyment Scale (PACES) (42) will be individually applied to the participants. This is a scale that has reported good reliability in children (Cronbach’s alpha of 0.96) (43), and it has even been used in other studies with this population (44, 45). The questionnaire will be applied referring to “when I participate in the active breaks…”.

Physical activity: ActiGraph wGT3X-BT accelerometers and the ActiLife 6 software will be used to measure the children’s level of physical activity, since this device is proven to have the validity and reliability to measure the physical activity level objectively in this age group (38). The accelerometers will be used during the school day prior to the intervention, in weeks 1, 3 and 6, in both the intervention and control groups. The accelerometers will be handed out and collected from the child at school at the beginning and end of each school day.

The accelerometers will be placed at the beginning of every school day, since the device is programmed and activated by an internal clock from the software so that it begins to record for the established time. The accelerometers are placed using an elastic belt at the intersection of the right hip and waist (on the iliac crest), as this is the place next to the center of gravity (39). Data from the participants who do not fulfill what is requested for the recording (days and hours) will not be analyzed. A short duration epoch of 15 s will be used; because the pattern, more intermittent the children’s physical activity (46), frequency of 100 Hz. The classification of the daily level of physical activity will be: sedentary, light, moderate, vigorous and moderate-vigorous, established from counts per minute. The cut-off point used will be determined by Evenson’s equation for the ActiGraph wGT3X-BT, especially used for students’ task classroom behavior (47) (sedentary 0–100 counts^x^min^−1^, light 100–2,295 counts^x^min^−1^, moderate 2,296–4,012 counts^x^min^−1^, vigorous 4,013 counts^x^min^−1^).

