### Statistical analysis

3.10

All the statistical analyses will be performed using jamovi software (50). The data will be reported as the mean and standard deviation for both experimental and control groups. Multilevel mixed-effects linear regression models will be used to assess the impact of the group (intervention vs. control) on the average scores of the physical activity level, on-task behavior and enjoyment of physical activity during whole intervention. Each variable will be fit by baseline levels of the corresponding variable and grouping by classes. All the analyses will control for the levels of physical activity at the beginning. All the analyses will be stratified by sex. We will consider the results statistically significant only if the *p* value will be lower than 0.05. We will calculate the effect size to examine the magnitude of any mean differences.

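### The stated 95% power for 54 students belongs to a calculation with independently randomised children, not to this two-school cluster trial or its planned model

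*Protocol article*

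**What the plan says.** Section 3.3 gives the settings of a G*Power run as "F-test, effect size = 0.25, α error = 0.05, power = 0.95" and the result: "According to this calculation, the participation of 54 students is estimated". It adds that "the sample is not large, however it has great power and can be representative of this group of students". It names no type of F-test, number of measurements, correlation, intracluster correlation (ICC) or design effect.

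The design is described elsewhere in the article:

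- The title calls the trial a pilot and cluster randomised.
- Section 3.1: "This study uses an experimental design with a pre-and post-test", and "The sample will be divided into two groups: intervention and control".
- Section 3.2 plans two schools, one per arm, chosen for viability, and 60 students.
- Section 3.7: "Three measurements will be assessed at weeks 1, 3 and 6: physical activity levels, on-task classroom behavior and enjoyment of physical activity". Section 3.7.3 has the accelerometers worn in both arms as follows: "The accelerometers will be used during the school day prior to the intervention, in weeks 1, 3 and 6, in both the intervention and control". This can be read as adding a measurement before the intervention.
- Section 3.10: "Multilevel mixed-effects linear regression models will be used to assess the impact of the group (intervention vs. control"). The outcome is the average score over the whole intervention, adjusted for its baseline value and grouped by class.

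**The concern.** The title and the analysis section acknowledge clustering, but the sample size leaves no room for it. The quantity tested may also differ. A pre-post interaction, the likeliest source of 54, is not the arm effect on a baseline-adjusted average.

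At stake is how the result is read. Section 3.10 sets a significance threshold of 0.05, and section 2 states an effectiveness aim. Set against a claim of 95% power, a null result would look like good evidence of no effect. The design cannot support that inference.

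**Working it through.** **Inputs from the article.** Effect size 0.25 (read as Cohen's f; the symbol is not given), alpha 0.05, power 0.95, N = 54, two groups, three outcome measurements, two schools, 60 planned. **Assumed because not given:** correlation between measurements, sphericity (epsilon), ICC.

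**1. Reproducing 54.** For a repeated-measures interaction (or within-factor) test with m measurements and correlation r, the noncentrality is lambda = N f² m/(1 − r).

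- m = 2, r = 0.5: lambda = 54 × 0.0625 × 2/0.5 = 13.5 with 1 and 52 df; power 0.9501. N = 52 gives 0.942, so 54 is the smallest even N. This fits the pre-post, two-group wording of section 3.1.
- m = 3, r about 0.37 to 0.38: also 54. At r = 0.5 it gives 44, or 54 again if epsilon is 0.75.
- One-predictor regression with f² = 0.25: lambda = 0.25 × 54 = 13.5; also 54.
- Not matching: between-factor repeated measures at r = 0.5 (158 for m = 2, 142 for m = 3) and one-way ANOVA or ANCOVA (210).

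Every matching route treats children as independent.

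**2. Power for the planned type of analysis, children still independent.** For two arms, f = 0.25 is d = 0.5. The mean of three post measures, adjusted for baseline, with all correlations equal to r, has residual variance (1 + 2r)/3 − r².

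- r = 0.5: 0.667 − 0.25 = 0.417; lambda = 54 × 0.0625/0.417 = 8.1 with 1 and 51 df; power about 0.80.
- r = 0.3: 0.533 − 0.09 = 0.443; lambda = 7.6; power about 0.77.
- r = 0.7: 0.8 − 0.49 = 0.31; lambda = 10.9; power about 0.90.

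With all 60 children analysed and r = 0.5, lambda = 60 × 0.0625/0.417 = 9.0 and power is about 0.84.

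**3. If the calculation was the two-measurement interaction.** The SD of a change score is √(2(1 − 0.5)) = 1 SD. With 27 per arm, a between-arm difference in change of 1.0 SD gives noncentrality 1²/(2/27) = 13.5, the same lambda. On this reading f = 0.25 means a 1.0 SD difference in change.

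Now let ICC be that of the pre-post change, with 27 children per school, so that the design effect is 1 + 26 × ICC:

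| ICC of change (assumed) | Design effect | lambda | Power |
|---|---|---|---|
| 0.02 | 1.52 | 8.88 | 0.83 |
| 0.05 | 2.30 | 5.87 | 0.66 |
| 0.10 | 3.60 | 3.75 | 0.48 |

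If these ICCs are instead cross-sectional, and school effects correlate c over time, the ICC of change is 2 × ICC × (1 − c). At c = 0.5 the table is unchanged. At c = 0.9 the ICCs of change are 0.004, 0.01 and 0.02, and power is about 0.93, 0.89 and 0.83. At c = 0 they are 0.04, 0.10 and 0.20, and power is about 0.71, 0.48 and 0.31.

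**4. One school per arm.** Two schools minus two arms leaves 0 df for between-school variance, so an ICC would have to come from outside the trial. Even with a known ICC, more pupils cannot remove the school component. For an unadjusted difference of 0.5 SD, the standard error tends to √(2 × ICC) as pupils increase. At ICC 0.02 this is 0.20, and power is at most Φ(0.5/0.20 − 1.96) = 0.71. At ICC 0.05 the standard error is 0.316 and the limit is 0.35.

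**5. Precision with 60 children, unadjusted.** The 95% CI half-width is 1.96 × √(4/60) = 0.51 SD ignoring clustering. At an assumed ICC of 0.05 with 30 per school, the design effect is 1 + 29 × 0.05 = 2.45, and the half-width is 0.51 × √2.45 = 0.79 SD.

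**The case against.** The strongest reply has four parts.

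- **It is a pilot with 60 planned, not 54.** A pilot needs no formal power, but this one claims it. The six extra children cover 10% loss (60 × 0.9 = 54). Sections 3.2.2 and 3.7.3 remove children with low attendance or incomplete accelerometer records from the analysis, so the margin may be used up.
- **The planned model is multilevel and baseline-adjusted.** This stands in part: adjustment and averaging bring power to about 80% under step 2, well above a single unadjusted measurement. Grouping by class does not separate school from arm.
- **Stable school differences cancel from change scores.** This stands. The 83%, 66% and 48% apply only when ICC means that of the change. The loss is smaller if school effects persist over time and larger if they do not.
- **The arithmetic is right.** This also stands: 54 reproduces. The fault is a mismatch between the basis of the sample size and the design.

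A reader might go further than the article allows. It does not show that a two-measurement repeated-measures ANOVA was run: only an F-test is named, and other routes give 54. It therefore does not show that a 1.0 SD difference was assumed. The requirement of 210 children belongs to an unadjusted or single-outcome test that is not the planned one. Nor does the article announce a main trial into which the figure would be carried.

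**Conclusion.** The point holds as a mismatch between the sample-size basis and the design. The 95% power and the claim of great power apply to independently randomised children under an unnamed F-test. They do not apply to two schools, one per arm, analysed on a baseline-adjusted average.

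Before any clustering, power for the planned type of analysis is about 80%. This rests on d = 0.5, 54 children and correlations of 0.5; it is 77% to 90% for correlations of 0.3 to 0.7. The size of the further loss from clustering depends on an ICC that the article does not give and that two schools cannot estimate. That no pupil-level calculation can support 95% power here does not depend on which F-test was run.

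**What to change.** Rewrite the sample-size paragraph of section 3.3:

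1. Remove the 0.95 power figure and the statement that the sample has great power and can be representative. Alternatively, state that 54 applies only to independently randomised children, name the test, number of measurements and correlation used, and say that clustering is not allowed for.
2. State that 60 is a feasibility size set by recruiting two schools.
3. Give precision under stated assumptions. For an unadjusted arm difference, the 95% CI half-width is about 0.51 SD ignoring clustering and about 0.79 SD at an assumed ICC of 0.05.
4. State that between-school variance cannot be estimated with one school per arm.

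The cost is one paragraph and a less favourable figure. No extra children are needed and trial conduct does not change.

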**Figure 2 fig2:**
[figure not shown]
Flow chart of participants through the ACTIVA-MENTE study.

### Intervention

3.4

The ACTIVA-MENTE program is based on other programs previously reported in the literature which performed active breaks at school using audiovisual material (videos) (21, 24). A preliminary consultation was done with the teachers or with the head of student well-being in elementary schools that had previously applied the ACTIVA-MENTE non-systematically. One representative school was consulted, with responses from 11 other schools of similar demographic characteristics. The consultation was done to assess the viability of introducing regular active breaks in elementary classrooms, based on the perception of the students and principals regarding these interventions. Of these teachers, most (n = 10 of 12) positively valued the implementation of the program, considering it feasible to perform the designed active breaks in the program regularly (several times a day during the day), and indicated satisfaction by the teachers and students. In addition, most of them (n = 11–12) perceived improvements in students’ disposition and attention post-break session. Another important element of the ACTIVA-MENTE program is that the activities do not require a special technological element. The proposed activities only use equipment already available in the classrooms (e.g., audio, projector), attending teachers reported needs, such as fast and easy activities implementation.

### ACTIVA-MENTE program

3.5

The program consists of teachers applying active breaks through previously recorded videos specially designed for the program. Online access to the program’s official website is free access: https://convivenciaparaciudadania.mineduc.cl/activamente/. These videos last 4 min and 30 s. This time is divided into 1 min of preparation (general explanation and indications), 3 min for 6 activities (e.g., jumps with feet together, skipping, jumping jacks, scissor kicks) of moderate-to high-intensity, i.e., over 60% maximum heart rate (HRmax) (32) the intensity will be monitored using the Polar OH1 device (Finland) and the rated perceived exertion scale (33) with a poster placed in front of the students when performing the break activities. Every activity is performed for 20 s with 10 s of recovery. During recovery time, the following activity is explained, the final 30 s are for the cool down (Table 1).

**Table 1 tab1:** Description ACTIVA-MENTE program.

Approaches	Organization: ACTIVA-MENTE video	Duration
In-person classes: students beside their desks	Beginning: general instructions	1 min
Teacher’s instructions to the class	Physical activity: 6 activities	3 min total
Instructions of the video guide	Execution of each activity (e.g., skipping, jumps)	20 s
Virtual classes: students are in front of a device (tablet, cell phone, computer)	Recovery and explanation of following activity	10 s
Instructions from the video guide	End: reincorporation to the other class activities	30 s
	Total time ACTIVA-MENTE	4 min 30 s

Min, minutes; s, seconds.

The online explanation of the activities execution is done by physical education teachers especially trained for this. The active breaks through videos are done in the middle of each class (for classes of 45 min the break is applied at minute 20), except physical education class, achieving six active breaks for day, during 6 weeks. There are 31 different videos that can be used interchangeably, the choice is up to the teacher (all the videos have the same structure). The activities suggested in the videos are based on previous studies (34–36) and the students can perform them standing up beside their desk. All the proposed activities can be adapted even for children with motor, auditory and/or visual disability (37). In addition, the program can also be implemented at online classes, using a platform that can share the video with the students (Figure 3).

**Figure 3 fig3:**
[figure not shown]
ACTIVA-MENTE model. **(A)** Active breaks during virtual classes for schoolchildren. **(B)** Active breaks during in-person classes for schoolchildren.

### Implementation, intervention fidelity and teacher training session

3.6

In order to improve the operation and adherence to the intervention protocol, a researcher will be present during the first 2 weeks to provide assistance. The research will provide the teachers with general support during the school visits to answer questions, adapt activities or give the teachers feedback. At the first week, both the researcher and the classroom teacher will implement the ACTIVA-MENTE activities together using the videos designed especially for the program. At week 2, the activities will be implemented only by the classroom teacher, while the researcher will observe and provide the feedbacks. Finally, at the third week, the classroom teacher will independently guide the ACTIVA-MENTE activities without the researcher presence. The teachers will be able to send e-mails or communicate at any time by telephone with the researchers if they have any concerns or they need more support. The use of the data collection instruments will be monitored by the researchers.

The fidelity of the program implementation will be evaluated by the use of accelerometers by children during school day in the first week (week 1), third week (week 3), and the last week of the intervention (week 6). The teachers will be instructed to complete a record of the daily application of ACTIVA-MENTE throughout the intervention period. Afterwards, a member of the research team will attend daily to collect the teachers’ records and to monitor the application of ACTIVA-MENTE. The data provided from the accelerometers will be compared with the teachers’ records at weeks 1, 3 and 6 of the intervention in order to verify the application of ACTIVA-MENTE. In the case of the teachers cannot perform the planned active break, they must indicate the reason. There will always be assistance staff available to remind the teacher of the application of active breaks.

One week before implementing the program, all the teachers will be trained for 45 min. The training session will be carried out in the schools by a researcher, who is a qualified elementary school teacher. The training session is designed to inspire and instruct the teachers with the necessary skills and knowledge to implement the ACTIVA-MENTE program. This training session content will include the importance to add physical activity times into the classroom routine; the evidence of current research that emphasizes the potential positive effect of active breaks to improve the physical activity levels and the on-task behavior; the explanation regarding the program; and finally, the instructions for program application. Since a researcher will be present during the first 2 weeks of implementation, extensive demonstrations of the active break activities will not be provided during the training session. After training session, the printed and the digital materials of ACTIVA-MENTE will be distributed, as well as a certification.

### Procedures, outcomes measures and data collection

3.7

Three measurements will be assessed at weeks 1, 3 and 6: physical activity levels, on-task classroom behavior and enjoyment of physical activity. The implementation will be carried out by a group of research collaborators properly trained by the research team during four sessions previous to the assessment on the application of the instruments. The evaluators do not know the students and in the research, they only carry out the data collection.

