**Figure 1 fig1:**
[figure not shown]
Standard Protocol Items: Recommendations for Interventional Trials (SPIRIT) (28). −*t*_1_, enrolment of the school and participants; 0, allocation of the groups and baseline assessments (high, weight, age); *t*_1_–*t*_6_, Intervention active breaks; t_1_, t_3_, t_6_ assessments; t_7_, post assessments (high, weight, age).

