On-task classroom behavior: Information will be compiled on the students’ behavior in the classroom individually and as a group. The observation will be done in weeks 1, 3 and 6, in the intervention and control groups. The members of the research team trained in the data collection instrument will make observations on the students’ behavior during a period of 15 min before and after participation in a break with ACTIVA-MENTE.

Individual classroom behavior will be measured using a tool adopted from the Direct Behavior Rating Scale (41). The Direct Behavior Rating Scale is a hybrid of behavior grading scales and direct observation. This observation tool requires the teacher to indicate for each child, on a scale from 1 (0%) to 10 (100%), the percentage of time they spend on the task, i.e., how committed they are to the task (e.g., listening to the teacher, writing, looking at instruction materials, etc.) during the observation period. This tool has evidence of reliability (r = 0.91) based on data from 617 elementary students from 44 classroom teachers (41).

Group behavior, otherwise, will be measured using a modified version of the Classroom Behavior and Assets Survey-Teacher, which is designed to provide the teacher’s perception of students’ behavior in class. The member of the research team trained in the instrument will indicate the proportion of the class that shows on-task behavior (as defined in the individual behavior assessment tool) during the observation period. The response options include: 0 (0 students), 1 (1–2 students), 2 (some students), 3 (approximately one quarter of the class), 4 (approximately half the class), 5 (approximately three quarters of the class), 6 (most of the class) and 7 (the entire class). Although there are few tools available to evaluate classroom behavior at class level, and a lack of information on reliability and validity, a modified version of this tool was used in a similar study, with evidence of reliability (alpha = 0.85) (13).

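### No pre-intervention on-task measurement is scheduled and the accelerometer baseline is inconsistent, yet the model adjusts for both

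*Protocol article*

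**What the plan says.** **What the model needs.** Section 3.10 fits a mixed model to the average of each outcome over the whole intervention, adjusted for the baseline of that same outcome. It adds: "All the analyses will control for the levels of physical activity at the beginning". Section 3.1 describes a pre- and post-test design.

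**What the schedule supplies.**
- Section 3.7, overview: "Three measurements will be assessed at weeks 1, 3 and 6: physical activity levels, on-task classroom behavior and enjoyment of physical activity".
- Figure 1 caption, time 0: "allocation of the groups and baseline assessments (high, weight, age", with the program running from t1 to t6 and assessments at t1, t3 and t6.
- Accelerometers, detailed procedure under 3.7.3, for either arm: "The accelerometers will be used during the school day prior to the intervention, in weeks 1, 3 and 6".
- On-task behavior, same section: "The observation will be done in weeks 1, 3 and 6, in the intervention and control groups". The observation window is "during a period of 15 min before and after participation in a break with ACTIVA-MENTE".
- Enjoyment (PACES), same section: weeks 1, 3 and 6, intervention group only, with items worded about taking part in the breaks.

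**What happens in week 1.** Section 3.6: "At the first week, both the researcher and the classroom teacher will implement the ACTIVA-MENTE activities together".

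**The concern.** The model calls for a covariate that the schedule does not clearly produce. For on-task behavior, no value from before the program is planned in the text. For physical activity, one passage implies such a value and the two general schedule statements omit it. Because initial physical activity enters every analysis, that one unclear clause also reaches the on-task model.

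Two things are at stake. First, an analyst who needs a baseline and has none may fall back on week 1, a week in which the intervention school is already doing the breaks. Adjusting for a value that treatment has changed removes part of the effect being estimated. Second, section 3.3 promises to adjust for differences found between the groups. With one school per arm and no on-task value from before the program, a prior difference between the schools on that outcome cannot be seen. An analysis plan cannot repair this afterwards, because it concerns when the data are collected.

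**Working it through.** **1. Baseline required against baseline scheduled**

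| Outcome | Baseline term in 3.10 | Pre-intervention value in the text |
|---|---|---|
| Physical activity (primary) | Yes, and in all analyses | Implied by the procedure under 3.7.3; absent from 3.7 and the Figure 1 caption |
| On-task behavior | Yes | None |
| Enjoyment (PACES) | Yes | None possible: the items ask about the breaks, and controls are not given the scale |

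**2. The plan's own figure.** Section 3.3 gives 54 students from an F-test with f = 0.25, alpha 0.05 and power 0.95. The number of measurements and the correlation are not stated. Assuming a two-group, two-measurement within-between interaction with correlation 0.5, the noncentrality is f²·N·m/(1 − ρ) = 0.0625 × 54 × 2 / 0.5 = 13.5 on 1 and 52 degrees of freedom. The power is 0.9501, so 54 is reproduced. At the same correlation, three measurements give 44 and four give 36. This fits a pre/post comparison but is weak support: with three measurements, N is 60 at correlation 0.3 and 44 at 0.5, so a value in between would also give about 54.

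**3. What would follow if week 1 served as baseline.** This is an illustration, because the protocol does not prescribe it. Assumptions: equal variances, the same correlation ρ between any two weeks, effect δ at weeks 3 and 6, and effect rδ at week 1. The documents give neither ρ nor r.

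- Week-6 outcome: the within-arm slope on week 1 is ρ. The adjusted effect is δ − ρ·rδ, so the share lost is ρr.
- Mean of weeks 1, 3 and 6: the unadjusted effect is δ(r + 2)/3 and the slope on week 1 is (1 + 2ρ)/3. The adjusted effect is δ[(r + 2) − r(1 + 2ρ)]/3 = 2δ(1 − ρr)/3, so the share kept is 2(1 − ρr)/(r + 2).

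| ρ | r | Lost, week 6 | Lost, mean of weeks 1, 3, 6 |
|---|---|---|---|
| 0.3 | 0.5 | 15% | 32% |
| 0.3 | 1 | 30% | 53% |
| 0.5 | 0.5 | 25% | 40% |
| 0.5 | 1 | 50% | 67% |
| 0.7 | 0.5 | 35% | 48% |
| 0.7 | 1 | 70% | 80% |
| any | 0 | 0% | 0% |

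Example for the last column at ρ = 0.3, r = 0.5: kept = 2(1 − 0.15)/2.5 = 0.68, so 32% is lost.

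**4. Simulation check.** With 200,000 children, ρ = 0.5, r = 1 and a true effect of 0.50 SD:
- week 6 adjusted for a true pre-intervention value: 0.504; adjusted for week 1: 0.256;
- mean of weeks 1, 3 and 6 adjusted for a true pre-intervention value: 0.500; adjusted for week 1: 0.168.

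These agree with the formulas (0.25 and 0.167 expected with the week-1 covariate).

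**The case against.** The strongest reply concerns the primary outcome. A reader might infer that every outcome is measured only on treatment and that the plan therefore discards much of its effect. The documents do not support that. Weeks 1, 3 and 6 lie inside the intervention, so the accelerometer wording "The accelerometers will be used during the school day prior to the intervention, in weeks 1, 3 and 6" reads most naturally as a list: once before, then three times during. The pre/post label in 3.1 and the reference in 3.10 to initial activity agree with that reading. The silence of 3.6 on a pre-intervention period is no evidence against it, because wear there serves to verify that breaks took place. The grid of Figure 1 cannot be seen, and its caption does not say that nothing else is measured at time 0. So for accelerometry the fault is an inconsistency, and prior differences between the schools in physical activity could be seen if the 3.7.3 wording is followed.

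Nor does any section name week 1 as the baseline. The loss figures describe a possible misuse, and the figures for the three-week mean also require week 1 to be covariate and part of the outcome at once. For PACES, attenuation does not arise, because there is no control arm to compare with.

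What the reply does not remove is the on-task gap. The 15 minutes before a break is a within-session value in weeks 1, 3 and 6. It is not defined as a baseline, and the control school takes no break to anchor it. Staff working from 3.7 or the Figure 1 caption alone would also have no instruction to collect accelerometer data before week 1.

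**Conclusion.** The point holds in a limited form. The model in 3.10 requires a baseline for each outcome. The text schedules none for on-task behavior, is inconsistent about the one for accelerometry, and cannot have one for PACES.

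The size of any bias is conditional. It arises only if week 1 is taken as the baseline, and it runs toward zero when the week-1 effect has the same direction as the later one. For ρ of 0.3 to 0.7 and r of 0.5 to 1, the loss is about 15% to 70% of a week-6 effect and 32% to 80% of the effect on the mean of weeks 1, 3 and 6. It is zero if week 1 shows no effect. All of these values of ρ and r are assumptions. The matter should be settled before field work starts, because a pre-intervention week that is missed cannot be recovered.

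**What to change.** - **3.7 and Figure 1:** align the schedule with the accelerometer procedure by stating a pre-intervention accelerometer period in both schools. Take the on-task rating in both schools in that same period, with the same staff. Since no break is delivered then, tie the observation window to a fixed point in the lesson.
- **3.10:** define only that pre-intervention value as the baseline covariate. State that week 1 is a post-baseline outcome and never a covariate. If no pre-intervention on-task value is collected, drop the baseline term for that outcome.
- **PACES:** remove it from the baseline-adjusted arm model, since it can have neither a baseline nor an arm comparison.

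**Cost:** one on-task observation period in each school, added to an accelerometer period that 3.7.3 already implies. The remaining changes are to wording only.
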